## Abstract

**Background:**

Previous study showed that both melatonin supplement and physical exercise intervention could improve sleep quality in children with autism spectrum disorders (ASD) with the increase in endogenous melatonin level. However, none of the studies have directly compared the effectiveness between the two interventions on treating sleep disturbance in children with ASD. Without direct comparison, we do not know which intervention is better. Thus, we designed a study to compare which intervention is more effective to treat sleep disturbance in children with ASD and to examine whether the combination of the two could be the most efficacious. We present a protocol for conducting a randomized controlled trial to compare the effectiveness of physical exercise and melatonin supplement on treating sleep disturbance in children with ASD.

**Study design:**

The proposed study will be a four-group randomised control trial (RCT) design, with equal allocation of participants to the three intervention groups and one control group.

**Methods:**

All eligible participants will be randomly allocated to a morning jogging group, a melatonin supplement group, a combination group and a control group. Changes in sleep quality will be monitored through actigraphic assessment and parental sleep logs. Melatonin levels represented by 6-sulfoxymelatonin will be measured from the participants’ 24-h and the first morning void urinary samples. All the assessments will be carried out before the intervention (T1), in the mid of the study (5 weeks after the commencement of the study) (T2) and after the 10-week intervention (T3). Level of statistical significance will be set at 5% (i.e. *p* < .05). The results of this trial will be submitted for publication in peer-reviewed journal.

**Findings:**

The findings will provide evidence to determine whether physical exercise or melatonin supplement or the combination of interventions is the most effective to treat sleep disturbance in children with ASD.

## Introduction

Autism spectrum disorder (ASD) is a neurodevelopmental disorder. In Hong Kong, the latest prevalence rate is 1.5% and the rate is predicted to increase [1]. Children with ASD are characterized, in varying degree, by deficits in social communication and social interaction, restricted and repetitive behavior, interests and activities. Moreover, children with ASD are also more susceptible to sleep disturbance than children with typical development (see Elrod et al. [2] for review). Common sleep disturbances in children with autism include delayed sleep onset, difficulty in sleep maintenance and insufficient sleep duration [2]. Given the importance of adequate sleep in child development, sleep disturbance in children with ASD is detrimental. Research shows that poor sleep is closely related to poor cognitive performance [3] (e.g., impaired learning performance, memory consolidation) and intensified behavioral problems [4] (e.g. increased stereotypic behavior) among children with ASD, which subsequently worsen quality of life of ASD individuals and their families [4]. As a result, developing effective intervention strategies are crucial.

To achieve so, we need to understand the causes of sleep disturbance in the population. Over decades, a growing body of literature has shown that physiological differences in children with ASD may be the major cause of sleep problems in children with ASD (see Maxwell-Horn et al. [4] for review). For example, children with ASD appear to have an increased state of physiological arousal than their TD peers [5], which is evidenced by higher heart rates during sleep, increased skin conductance at rest condition and after auditory stimulation, as well as lower melatonin production than their TD counterparts [6]. Currently, parent-directed behavioral sleep interventions (e.g., extinction, fade bedtime) are recommended as first-line treatment for sleep disturbance in ASD [7]. However, these types of intervention are very intensive and may sometimes be very stressful to both children and parents (e.g. extinction intervention [8]). Moreover, evidence for the intervention efficacy remains largely inconclusive due to small sample sizes and lacked follow-up data on sustainability [9]. If the behavioral intervention does not improve the problem, then the use of pharmacologic treatment is generally considered by clinician and parents. Given the decreased melatonin secretion as mentioned earlier, melatonin supplement—a nutritional supplement with sleep-promoting and sleep phase shifting properties, has gained widespread public acceptance as an alternative to FDA-approved medications due to its favourable side-effect profile and relatively low cost [10]. Several meta-analyses have also provided supportive evidence that melatonin supplement positively impacts sleep in children with autism, including reduced sleep onset latency, increased total sleep duration and improved sleep efficiency [11]. Despite favourable evidence on the use of melatonin supplement, it is still wise to “start low and go slow” when turning to this intervention [5], particularly given reports of adverse events such as somnolence, headache, daytime drowsiness and fatigue in some children [7]. Therefore, researchers are exploring other non-behavioral and non-prescription pharmaceutical approaches with undesirable side effects to treat sleep problems in children with ASD. One intervention that has received growing attention is physical exercise.

Over the past decade, a significant body of research has investigated the effects of physical exercise on sleep and the results generally supported the positive impact of physical exercise on sleep (see Kelley et al. [12] for review). Previous studies also support the sleep benefits of physical exercise in children with ASD. For example, we have examined the impact of a basketball training intervention on sleep quality (sleep efficiency and wake after sleep onset) and cognition (inhibition control and working memory) in 40 children with ASD [13]. Research revealed a significant improvement in sleep efficiency and reduction in wake after sleep onset time in the intervention group but not in the control group [13]. Similar sleep benefits following physical exercise were also evident in a more recent study [14], where we showed that jogging intervention had significantly improved sleep efficiency and sleep duration in children with ASD. More remarkably, we also observed that the endogenous melatonin level, as reflected by the 6-sulfatoxymelatonin (aMT6s), was significantly increased within the jogging intervention group, while no change was found in the control group. Physical exercise appears to be capable of modulating the endogenous melatonin level in children with ASD, which in turns improves their sleep quality. If it is so, it is then natural to ask which intervention (i.e. physical exercise or melatonin supplement of the combination of two) is more effective in treating sleep disturbance improving the sleep quality of children with ASD. Without direct comparison, this question remained unanswered. Therefore, here we propose a new study protocol.

This study protocol has two objectives: (1) to determine which intervention is more effective in improving sleep quality in children with ASD and 2) to explain how these interventions impact on sleep via melatonin-mediated mechanism model. We hypothesise that the combination intervention (i.e. jogging and melatonin supplement) is the most effective because it may provide sufficient melatonin level to enhance sleep quality through both physical exercise and melatonin supplement.

## Methods/Design

### Study design

The proposed study will be a single blinded four-group randomised control trial (RCT).

### Participants

Participants will be screened using the following inclusion criteria: (1) clinical diagnosis of ASD by a physician based on the Diagnostic and Statistical Manual of Mental Disorders, 5th edition, (DSM-5) [15]; (2) age 8–11 years; (3) pre-puberty as indicated by Tanner stage I through screening by a physician (to prevent any puberty influence on hormonal response); (4) being given an average of 8 hours of sleep per night by their parents over the past 3 months; (5) parents reported sleep onset delays of 30 minutes of longer on three or more nights per week; (6) free of psychotropic medications (allergy medications and medications for constipation are allowed); (7) non-verbal IQ over 50 using a brief version of Wechsler intelligence scale for children (Chinese revised, C-WISC) [16] (since lower IQ is liked to higher prevalence of comorbid psychiatric disorders and seizures); (8) Social Response Scale T-score 80 or above (to control for the ASD severity) and (9) no concurrent medication for at least three months before the study or any prior melatonin treatment.

Exclusion criteria are: (1) with one or co-morbid psychiatric disorders; (2) with other medical conditions that limit their physical exercise participation and sleep (e.g., asthma, seizure, cardiac disease etc); and (3) with a complex neurologic disorder (e.g., epilepsy, phenylketonuria, fragile X syndrome, tuberous sclerosis) and (4) participants who are currently meeting physical exercise guidelines (i.e. 60 minutes of moderate and vigorous physical exercise each day).

### Intervention

Each participant will attend 3 one-week-long assessments in their respective schools, where we will assess their habitual sleep patterns and endogenous melatonin level before the intervention (T1), in the mid of the study (5 weeks after the commencement of the study) (T2) and after the 10-week intervention (T3). The mid-assessment is valuable to know how much variance in sleep behaviors is accounted by variance in melatonin, as well as to assess the adherence of the interventions. SPIRIT schedule of the study and a flow diagram of the study are shown in Figs 1 and 2 respectively. The estimated starting date of the study will be 1^st^ August, 2022 and the estimated ending date will be 30^th^ June, 2023.

**Fig 1 pone.0270428.g001:**
[figure not shown]
SPIRIT schedule of enrolment, interventions, and assessments of the study.

**Fig 2 pone.0270428.g002:**
[figure not shown]
Flow diagram of the study.

#### Intervention A—Morning jogging group

The training protocol, assessment and instructional technique will be referenced on our previous protocol in children with ASD [17]. However, we will modify the frequency of the jogging sessions to suit the comparison with other intervention group (i.e. intervention B and C). This intervention will be a 10-week jogging program consisting of 50 sessions (5 sessions per week, 30 min per session) in each participating school. The increase of jogging sessions from the previous protocol [17] is to make the prescription equivalent to the melatonin supplement prescription for other interventions (B and C), which will be prescribed to the participants every day, according to the previous protocol [17]. Moreover, this is more close to the World Health Organization (WHO) recommendation that everyone should participate in physical exercise daily. Meanwhile, the jogging program is confined to morning sessions based on the favourable sleep outcomes from previous study [18]. To counteract the possible influence of natural sunlight exposure, all jogging sessions will be confined to indoor setting. Each intervention session will be administered by a trained research assistant assisted by student helpers. All the research staff (i.e. student helpers and research assistant) will be required to attend a workshop to standardize the procedure on implementing the intervention, as well as handling and motivating their ASD partners. Each session will be conducted in an identical format with 5 minutes of warm-up activities, followed by 20 minutes of jogging (intervention), and 5 minutes of cool-down activities. In the jogging activity, participants will be asked to jog side-by-side with the research staff around an activity circuit (57m x 50m) marked with 4 red cones. Participants are instructed to jog at a moderate intensity level. The intensity level of jogging will be measured by heart rate monitor (Polar H1). Considering the general low physical fitness of children with ASD, physical exercise with a heart rate above 50% of the maximum heart rate (subtracting the participant’s age from 220) is regarded as moderate intensity. Motivation techniques (e.g. verbal cue, visual chart, favourite post-intervention activity) will be used to enhance the compliance rate. Meanwhile, questionnaire will be given to the research staff assisting the jogging intervention to assess the adherence of the intervention at T2. The feasibility, community-viability and sustainability of the exercise intervention are confirmed with previous research experience and the cooperation of the participating schools. Since these intervention sessions are conducted in the morning hours before school start times, the participants may get less sleep time since they must arrive at school early enough to do the exercise. To ensure the participants to have sufficient sleep, they are strongly encouraged to go to bed earlier at night.

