
#### Intervention B—Melatonin supplement group

Participants in this intervention group will undergo a 10-week melatonin supplement intervention period, where melatonin supplement (Natrol®, Chatsworth CA) will be provided 30 minutes before bedtime [19]. The prescription time (i.e. 30 minutes before bedtime) and the dosage of 3mg will be used because these are optimal for most of the participants as suggested by Malow and colleagues [19]. 1 mg and 9 mg are not suggested to ensure the effectiveness of the intervention while preventing the potential daytime sleepiness. Similar to the aforementioned intervention, adherence of the intervention will be assessed at T2.

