### Statistical methods

All statistical analyses will be conducted using SPSS (version 26.0) for Windows (SPSS Inc., Chicago, IL, USA). All the data will be entered into SPSS by the research assistant. One-way (4 Groups: physical exercise vs melatonin supplement vs combined exercise and melatonin supplement vs placebo-control) analysis of variances (ANOVA) with repeated measures will be performed to compare changes in actigraphy data and endogenous melatonin level between and within groups over different time points (i.e. T1-T3). Post-hoc analyses will be performed when any significant difference both between- and within-group is found in any of the outcome variables. Bonferroni correction will be used to adjust the alpha levels. Depending on the proportion of missing data and the assumption of normality, multilevel regression or a generalized estimating equation (GEE) will also be used as a sensitive analysis to assess the effects of the physical exercise intervention, melatonin supplement, time effect, and their interaction with sleep outcomes and melatonin level outcomes if there is any missing data. Average time spent in both daily sedentary activity and MVPA at baseline will be used as covariates. Linear regression will be used to analyse the association between participant’s adherence to the intervention and the outcome variables as a secondary analysis. Mediation analysis will be conducted to examine the mediating effect of endogenous melatonin level at T2 on the relation between physical exercise and sleep at T3. Preacher and Hayes’ bootstrapping and conditional process modeling will be used to determine the significance of the mediating effect. A p-value of <0.05 will be considered statistically significant. Both proposal analysis and intention-to-treat analysis will be carried out. Demographic variables (e.g. age, sex, BMI) will be adjusted if they demonstrate clinically significant prognostic effects on the outcomes (with absolute correlation or Cohen’s d effect size of >0.2) for both main analysis and mediation analysis.

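### Adherence is assessed at T2, week 5 of 10, and no later check is stated, so the secondary adherence regression for T3 outcomes would rest on at most half the exposure

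*Protocol article*

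**What the plan says.** The Intervention section of the protocol article sets the mid-assessment and the final one "in the mid of the study (5 weeks after the commencement of the study) (T2) and after the 10-week intervention (T3". One stated purpose of the mid-assessment is "as well as to assess the adherence of the interventions".

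Each active group's section then repeats that timing:

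- **Jogging (Intervention A):** the programme is a "10-week jogging program consisting of 50 sessions (5 sessions per week, 30 min per session"), and a "questionnaire will be given to the research staff assisting the jogging intervention to assess the adherence of the intervention at T2".
- **Melatonin (Intervention B):** "Participants in this intervention group will undergo a 10-week melatonin supplement intervention period", and "Similar to the aforementioned intervention, adherence of the intervention will be assessed at T2".
- **Combination (Intervention C):** adherence is likewise placed at T2.

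The Study measures section has the outcomes measured at T1, T2 and T3. The Statistical methods section says: "Linear regression will be used to analyse the association between participant’s adherence to the intervention and the outcome variables as a secondary analysis". It names no outcome time point for that regression. It also plans a second analysis next to intention-to-treat, printed as a proposal analysis, which I read as per-protocol.

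**The concern.** The adherence measure and the final outcome cover different periods. T3 outcomes follow ten weeks of intervention, but an adherence value taken at T2 can describe only the first five. A child who complies until week 5 and then stops has the same value as one who complies throughout.

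Two analyses are exposed. The first is the secondary regression, whose slope for T3 outcomes would be read as the effect of adherence to the programme when the predictor holds only its first half. The second is the per-protocol set at T3, if one is intended, since compliance after week 5 could not be established from a T2 measure. An analysis plan written later cannot repair either, because it cannot supply data that were never collected.

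**Working it through.** **Exposure covered by a T2 measure**

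- Jogging (Intervention A section): 10 weeks × 5 sessions = 50, which reproduces the stated total. By T2: 5 × 5 = 25. Coverage is 25/50 = 50%.
- Supplement (Intervention B section for the 10 weeks; Intervention A section for daily prescription): 10 × 7 = 70 days. By T2: 5 × 7 = 35. Coverage is about 35/70 = 50%.

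These are upper limits. The five weeks are counted from the commencement of the study; if that means the baseline assessment rather than the first session or dose, coverage is lower.

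**Effect on the T3 regression**

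The documents give nothing on how stable adherence is, so the following inputs are assumptions:

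- X₁ and X₂ are adherence in weeks 1–5 and 6–10, and the T3 outcome depends on their mean M = (X₁ + X₂)/2.
- ρ is the correlation of X₁ with X₂, taken from 0.1 to 0.9.
- k is the ratio SD(X₂)/SD(X₁), taken as 1 or 2.

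If the true slope on M is β, regressing on X₁ alone gives β × cov(M, X₁)/var(X₁), so

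slope factor = (1 + ρk)/2.

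The correlation of X₁ with whole-course adherence is

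(1 + ρk)/√(1 + k² + 2ρk).

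| ρ | Slope factor, k = 1 | Correlation, k = 1 | Slope factor, k = 2 | Correlation, k = 2 |
|---|---|---|---|---|
| 0.1 | 0.55 | 0.74 | 0.60 | 0.52 |
| 0.3 | 0.65 | 0.81 | 0.80 | 0.64 |
| 0.5 | 0.75 | 0.87 | 1.00 | 0.76 |
| 0.7 | 0.85 | 0.92 | 1.20 | 0.86 |
| 0.9 | 0.95 | 0.98 | 1.40 | 0.96 |

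Worked entries: ρ = 0.5, k = 1 gives (1 + 0.5)/2 = 0.75; ρ = 0.9, k = 2 gives (1 + 1.8)/2 = 1.40. A simulation with 200,000 draws per cell agreed with the slope factors to within 0.003.

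With equal spread the slope is understated. If adherence spreads out in the second half, it can be understated, unchanged or overstated.

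**Illustration of lost precision**

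Take n = 40 children and a true correlation of 0.4 between the T3 outcome and whole-course adherence (both assumed). By the Fisher approximation, power = Φ(arctanh(r)·√(n − 3) − 1.96).

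- Whole-course adherence: arctanh(0.4) × √37 = 0.424 × 6.083 = 2.58, so power is Φ(0.62) = 73%.
- T2 measure, k = 1: r becomes 0.4 times the correlation in the table, and power is 46% at ρ = 0.1, 59% at ρ = 0.5 and 71% at ρ = 0.9.

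**The case against.** **T2 is not said to be the only time.** The article never uses that word, the SPIRIT schedule is a figure that is not shown, and attendance sheets or unit counts are details an article may leave to the full protocol. This stands as a caution. But the text is not silent on timing: the general Intervention section and all three active-group sections place adherence at T2. If the schedule lists a later check, these sections should be brought into line with it.

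**Jogging is supervised throughout.** Staff run every session beside the children, intensity is measured by heart rate monitor, and the team meets regularly to check delivery. This largely stands. A reader might infer that weeks 6–10 are wholly unobserved, and for jogging that goes too far: staff would see a child drop out of the sessions. What is missing is a stated adherence record for those weeks. Heart rate is described as a measure of intensity only, and it says nothing about supplement intake.

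**The regression may concern T2 outcomes, or early adherence as a predictor of T3.** Both are legitimate, and the second resembles the planned mediation analysis, which relates T2 melatonin to T3 sleep. But the section limits itself to neither, and early adherence answers a different question from adherence to the 10-week programme.

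**Nothing shows that adherence will fall.** This stands. A reader might take the 25% attrition allowance as evidence of fading adherence, but it concerns loss from the trial, not compliance among those who stay. Motivation techniques do not predict decline either, and the Placebo control group section reports high compliance in an ongoing study.

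**Conclusion.** The point holds as a limitation of secondary analyses and should be acted on. As written, the adherence measure covers at most 25 of 50 jogging sessions and about 35 of 70 dosing days. That is too little for a T3 adherence regression or a T3 per-protocol set. The weakest place is the supplement, given at bedtime and presumably at home, without staff present.

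The size of the distortion is not known. Over the assumed correlations of 0.1 to 0.9, the slope factor is 0.55 to 0.95 with equal spread and 0.60 to 1.40 if the later spread doubles. If adherence is very stable and equally spread, little is lost. These figures also assume that both halves count equally towards the T3 outcome.

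Two stronger conclusions are tempting and not supported. One is that the slope must be attenuated, which follows only under conditions such as equal spread. The other is that the comparison of interventions, the first objective, is compromised. The between-group and intention-to-treat analyses do not use the adherence measure, and any waning of adherence is part of the effect that intention-to-treat estimates. At most, a small or null T3 difference becomes harder to explain. Regressions of T2 outcomes on T2 adherence are unaffected.

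**What to change.** 1. **Jogging and combination groups:** record attendance and heart rate at each of the 50 sessions. Define adherence as the proportion attended, and the proportion reaching the intensity threshold the protocol already states.
2. **Melatonin, combination and placebo groups:** have parents keep a dosing tick-sheet, and collect it with a count of returned units at both T2 and T3.
3. **Statistical methods:** name the outcome time points for the adherence regression. Use weeks 1–5 adherence for T2 outcomes and weeks 1–10 for T3 outcomes, and base any per-protocol set at T3 on the weeks 1–10 record.

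Coverage then rises to 50 of 50 sessions and 70 of 70 dosing days, and the slope factor in the calculation becomes 1. The cost is slightly more record-keeping for staff at sessions they already run, and for parents, with collection at assessments that already exist. No treatment, visit or primary analysis changes.
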